#### 2.5.3 Data collection

##### 2.5.3.1 Primary outcomes

###### 2.5.3.1.1 Assessment of the trunk and hamstring muscle fatigue

Electromyography signals from the hamstring and trunk muscles will be recorded using the Delsys Trigno™ wireless EMG system. These muscles will be the erector spinae muscles at level L1 (Elfving et al., 2002a), the lumbar multifidus at the L5 level (Larivière et al., 2003), and medial hamstring muscles (Fiebert et al., 1997). These measurements will be taken at baseline, post-fatigue protocol, and post-recovery modalities (immediately and after 15 min). Following skin abrasion and cleansing with alcohol, electrode pairs will be placed bilaterally on the targeted muscles (Elfving et al., 2002b). The inter-electrode distance will be 2.5 cm (Areeudomwong et al., 2012a) on erector spinae muscles and the lumbar multifidus. The electrode for the medial hamstring will be positioned midway between the ischial tuberosity and the medial epicondyle of the tibia. During the tests for maximum isometric strength of the back extensor and hamstring muscles, sEMG recordings will respectively be collected from the multifidus and longissimus muscles (erector spinae), as well as from the medial hamstring muscles. Each sEMG measurement episode will have a standardized duration of 5 s, during which continuous recording occurs. The raw sEMG signals will be recorded with a sampling frequency of 2000 Hz and the bandwidth of sEMG will be around 20Hz–450 Hz (Larivière et al., 2003). The characteristics of muscle fatigue detected by EMG include a shift from a high-frequency spectrum to a low-frequency spectrum and an increase in amplitude (Sakurai et al., 2010). The assumption is that recovery and fatigue are mutually exclusive. Therefore, the shift from a low-frequency spectrum to a high-frequency spectrum and a decrease in amplitude are indicative features of muscle recovery detected by EMG. In this study, the absolute values of the frequency features (median frequency MDF, and mean power frequency, MPF) and the mean amplitude (root mean square, RMS) of the sEMG signals during the middle 3 s of the 5-s testing period will be employed to assess muscle fatigue and recovery. To ascertain these variables, the raw EMG signal will undergo processing using a fast Fourier transformation.

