###### 2.5.3.1.2 Assessment of the postural and core stability

The participants will stand on a force plate without shoes, with their arms naturally hanging by their sides. They will be asked to maintain an upright position with one foot directly in front of and touching the other foot. Participants will self-select the forward foot. Postural stability measurements will be taken at baseline, post-fatigue protocol, and post-recovery modalities (immediately and after 15 min).

Trials will be conducted under a variety of conditions in a randomized order: (1) Tandem stance on a force plate with eyes open, (2) Tandem stance on a force plate with eyes closed, (3) Tandem stance on a foam mat (Airex Balance Pad) positioned on the force plate with eyes open, (4) Tandem stance on a foam mat (Airex Balance Pad) situated on the force plate with eyes closed (Zemková et al., 2016). Each participant will complete one set lasting 30 s under each condition. There will be a short break between every two trials (Zemková et al., 2021a).

####### 2.5.3.1.2.1 Measurement of center of pressure (CoP) variables under stable and unstable conditions

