The FiTRO Sway Check (FiTRONiC, Bratislava, Slovakia) will be utilized for conducting an assessment of postural stability. The system detects the real force at the corners of the force plate and computes the instantaneous CoP position. It operates at a sampling rate of 100 Hz, with a 12-bit analog-to-digital signal conversion. The resolution of the CoP position is finer than 0.1mm, and it can measure within a range of 0–1,000 units per second. Non-linearity is within ±0.02% of the full scale, with a combined error of 0.03%. Sensitivity is at 2 mV/V±0.25%, and each sensor has an overload capacity of up to 150% of its range. Repeated measurements showed that reliability of CoP variables is consistently high, ranging from good to excellent, with no noteworthy fluctuations observed across consecutive days. The Romberg quotient, which involves calculating the sway ratio with eyes closed *versus* eyes open (EC/EO), will also be computed. Postural stability variables will be recorded using the FiTRO Sway Check (FiTRONiC, Bratislava, Slovakia) during unstable conditions. The apparatus comprises a square platform upheld by four springs possessing an elasticity coefficient of 40N/mm. When the center of pressure is shifted horizontally, the body weight distribution changes at the four corners of the platform. The force at each corner is determined by multiplying the spring’s elasticity coefficient by the vertical distance measured using a precise sensor. Analog signals are converted to digital (AD-converted) and sampled by computers at a rate of 100 Hz. Calculations of the instantaneous CoP position relies on the distribution of force across the four corners of the platform. Basic parameters of postural stability (i.e., mean CoP displacements in medio-lateral and anterior-posterior directions and mean CoP velocity) will be analyzed (Zemková et al., 2021b).

####### 2.5.3.1.2.2 Measurement of center of mass (CoM) variables under stable and unstable conditions

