Concurrently, the Gyko inertial sensor system (Microgate, Bolzano, Italy) will be employed to evaluate center of mass (CoM) variables. These sensors will be fastened with an elastic belt on the participant’s posterior trunk, close to the body’s center of mass. The height of the Gyko device positioned on the trunk will be adjusted prior to measurement to mitigate any potential influence on the collected data. The Gyko system comprises a 3D accelerometer for measuring linear accelerations experienced by the device, a 3D gyroscope for measuring the device’s angular velocities, and a 3D magnetometer for measuring the magnetic field surrounding the device. It provides data measurements at a frequency of up to 1,000 times per second (1 kHz), ensuring a high temporal resolution of the collected data. Using these data as a foundation, specialized software algorithms are employed to delineate the kinematics of the analyzed body segment. It calculates three primary measures of body sway: sway travel speed, sway length and area, and sway frequency (Zemková et al., 2021a).

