### 2.7 Statistical analysis

The statistical analysis will employ SPSS Statistics software (Version 24; IBM Corporation^©^, United States). To evaluate the normality of core and postural stability, as well as EMG variables, a Shapiro-Wilk test will precede any comparative analyses. For normally distributed data, a two-way ANOVA will be applied to explore the main effects of recovery modalities and time intervals, along with any potential interactions between these factors. The factors under consideration include the type of conditions [trunk stabilization exercises session, foam rolling exercise session, passive recovery] and testing time [T1: baseline, T2: immediately after modified Abt’s fatigue protocol, T3: immediately after recovery modalities, and T4: 15 min after recovery modalities]. To identify significant differences, Bonferroni *post hoc* comparisons will be conducted as necessary.

For non-normally distributed data, nonparametric tests will be utilized. Friedman’s test, followed by Dunn’s *post hoc* test, will be employed to compare core and postural stability, as well as EMG variables across testing times [T1, T2, T3, and T4]. The Kruskal-Walli’s test will be utilized for between-condition mentioned above comparisons at each testing time.

Data will be presented as mean ± standard deviation (SD). Effect sizes for both between-session and within-session comparisons of all quantitative variables will be evaluated using Cohen’s d coefficient: small effect (d < 0.2 and ηp2 = 0.01); moderate effect (d ≈ 0.5 and ηp2 = 0.06); and large effect (d > 0.8 and ηp2 = 0.14) (Cohen, 2013). The significance level (α) will be established at 0.05 for all statistical tests.

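### All EMG, CoP and CoM variables (about 33 to 52) are primary and each is tested at 0.05; no variable decides the question and the error rate across them is uncontrolled

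*Protocol article*

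**What the plan says.** The heading "2.5.3.1 Primary outcomes" covers three groups of variables, and none is singled out.

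- **EMG (2.5.3.1.1).** Three muscles are recorded: erector spinae at L1, multifidus at L5 and medial hamstrings. The text adds that "electrode pairs will be placed bilaterally on the targeted muscles". The features are "median frequency MDF, and mean power frequency, MPF) and the mean amplitude (root mean square, RMS) of the sEMG signals".
- **CoP (2.5.3.1.2).** There are four tandem stances (firm or foam surface, eyes open or closed), and "Each participant will complete one set lasting 30 s under each condition". The parameters are "mean CoP displacements in medio-lateral and anterior-posterior directions and mean CoP velocity". A Romberg quotient is added.
- **CoM (2.5.3.1.2).** For the inertial sensor: "It calculates three primary measures of body sway: sway travel speed, sway length and area, and sway frequency".

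Section 2.7 gives each variable a two-way ANOVA, three modalities by four times, with both main effects and the interaction. If data are not normal, it uses Friedman across times and Kruskal-Wallis between conditions at each time. Bonferroni and Dunn appear only as post hoc comparisons. The closing rule is "The significance level (α) will be established at 0.05 for all statistical tests".

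Section 2.4 sizes the trial for one repeated-measures test at 0.05 (f = 0.25, power 0.80, correlation 0.70) without naming an outcome. The Introduction and Section 2.1 give the aim as comparing the immediate effects of the two exercises.

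**The concern.** When every variable is primary and each carries its own 0.05, the plan does not say which result answers the question. Post hoc Bonferroni limits error among the pairwise comparisons of one variable. It does nothing for error across variables.

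The article's aims make this matter more. The Abstract expects the two exercises to be equally effective, the Introduction expects both to produce significant improvement, and the Discussion asks which of them is better. With dozens of primary variables and two assessments after recovery, a mixed pattern of results could be described as supporting any of these. The Introduction and Discussion would use a favourable result to suggest that core-specific exercise can be dropped at work, so the primary conclusion should have a known error rate.

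**Working it through.** **1. The plan's own figure.** Section 2.4 reports seven subjects, raised to 20 by choice. For a within-factor test, λ = N·m·f²/(1 − r), with df m − 1 and (N − 1)(m − 1) for one group. The number of measurements m is not stated.

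| m | N for power 0.80 |
|---|---|
| 3 | 17 |
| 4 | 15 |
| 12 (all 3 × 4 cells) | 8 (power 0.825; N = 7 gives 0.748) |

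Seven is therefore reproduced only approximately, and only at m = 12. A within-between interaction with 3 groups and 4 measurements gives 19, rounded up to 21 = 3 × 7, but that is not the test named. The present point does not depend on this. What matters is that the calculation covers one test at 0.05, with no allowance for many primary variables.

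**2. Count of primary variables (inferred from the lists).**

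| Group | Base count | Low | High |
|---|---|---|---|
| EMG | 3 muscles × 2 sides × 3 features = 18 | 9 (sides averaged) | 18 |
| CoP | 3 parameters × 4 stances = 12 | 12 | 12 |
| CoM | 3 measures × 4 stances = 12 | 12 | 16 (length and area separate) |
| Romberg | not counted | 0 | 6 (3 parameters × 2 surfaces) |
| **Total** | **42** | **33** | **52** |

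**3. Expected false positives.** With one test per variable and all nulls true, the expectation is 0.05 × K, whatever the correlation: 33 → 1.65, 42 → 2.1, 52 → 2.6.

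**4. Chance of at least one, if independent.** 1 − 0.95^K: 33 → 0.816, 42 → 0.884, 52 → 0.931.

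**5. Chance of at least one, if correlated (K = 42).** The article gives no correlation between variables, so the values below are assumed. The first column uses equally correlated normal test statistics. The other two simulate the planned 3 × 4 within-subject ANOVA with N = 20 and no effects (2000 runs per setting).

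| Common correlation | Normal model, one test | ANOVA, interaction only | ANOVA, modality or interaction |
|---|---|---|---|
| 0.3 | 0.76 | 0.77 | 0.95 |
| 0.5 | 0.58 | 0.60 | 0.84 |
| 0.7 | 0.38 | 0.40–0.44 | 0.68 |
| 0.9 | 0.19 | 0.21 | 0.35 |

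If variables correlate only within the EMG, CoP and CoM groups, the interaction test alone gives 0.75, 0.62 and about 0.4 at 0.5, 0.7 and 0.9. Counting both tests gives 0.94, 0.84 and 0.65.

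**6. Cost of correcting across all 42.** Bonferroni gives 0.05/42 = 0.00119. At N = 20, f = 0.25 and r = 0.70, power falls from 0.870 to 0.385 (m = 3) or from 0.927 to 0.531 (m = 4). One named primary keeps the full 0.05.

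**The case against.** Several objections have force.

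- **The count is inferred.** The article labels a heading primary and never states a number. It does not say that left and right EMG are analysed separately, and the CoM sentence describes what the device computes, so its word primary is not an endpoint label there. A reader might infer that at least 42 variables are designated. The text does not support 42 as a minimum, because averaging sides gives 33 before Romberg quotients.
- **A chance finding need not be likely.** MDF and MPF come from the same spectrum, and CoP and CoM are recorded in the same trials, so correlation may be high. With one test per variable the chance drops below one half at a common correlation of 0.7 and to about 20% at 0.9. A reader might take 88% as the error rate, but that figure requires independence.
- **The contrast and time are stated.** The aim gives both in words. What stands is that Section 2.7 does not carry them into a primary test and no variable is chosen.
- **Selective reporting is not planned.** No rule allows success to be claimed on whichever variable turns out significant. Under the Abstract's hypothesis of equal effectiveness, a false difference between the exercises would count against the claim. The rates above concern claims of difference and say nothing about equivalence.
- **A separate analysis plan may exist.** It could order the endpoints. But the article itself makes the primary/secondary split and itself fixes 0.05 for every test, so the point concerns a stated rule, not missing detail.

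**Conclusion.** The point holds in this form: about 33 to 52 variables share primary status, each is tested at 0.05, nothing controls error across them, and the stated contrast and time are not made primary in the analysis.

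Under a global null with one test per variable, about 1.7 to 2.6 false positives are expected. The chance of at least one is a range that depends on assumptions: for 42 variables, 88% under independence down to about 20% at a common correlation of 0.9. Even that lower end is about four times the nominal 5%. Counting the modality and interaction tests together raises it to 35% at the same correlation.

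The documents do not support saying that a spurious primary result is likely in every case, or that the trial intends to pick its endpoint afterwards. The correction should be made before analysis, and it is cheap.

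**What to change.** In Sections 2.5.3 and 2.7:

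1. Name one primary variable from the postural and core stability set, for example mean CoP velocity in one specified stance. The sponsor should justify the choice, including how it represents both core and postural stability.
2. Make the primary contrast foam rolling versus trunk stabilization on the change from T2 to T3, or on T3 adjusted for T1 and T2, tested at 0.05. A raw T3 difference would not measure recovery from fatigue.
3. Make the remaining CoP, CoM and EMG variables secondary. Either apply Holm within each family, or report estimates with confidence intervals and no confirmatory claim. Keep EMG as a secondary measure of recovery, since Section 2.5.3.1.1 uses it for that as well as for fatigue, and average left and right sides.
4. State that a non-significant difference will not be read as equivalence. A difference test at 0.05 cannot support the Abstract's hypothesis of equal effectiveness.

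**Cost.** Most variables lose primary status, and Section 2.4 must be restated for the chosen contrast. As a guide, the Section 2.4 inputs applied to a two-condition comparison (m = 2, N = 20) give λ = 20 × 2 × 0.0625/0.30 = 8.33 and power of about 0.78. This assumes that f = 0.25 and r = 0.70 carry over to the recovery measure, which the article does not show.

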## 3 Discussion

Comparing the immediate effects of trunk stabilization exercises to foam rolling exercises provides valuable insights into the efficiency of these two modalities for recovering impaired core and postural stability induced by fatigue in sedentary adults. Prolonged sitting leads to continued contractions of the trunk muscles, resulting in fatigue (Waongenngarm et al., 2016; Waongenngarm et al., 2018; Saiklang et al., 2022a; Saiklang et al., 2022b). Under fatigue, neuromuscular deficits can increase, potentially affecting core and postural control (Jabłońska et al., 2021; Zemková et al., 2021b). Shortness of the hamstring muscle and the posterior pelvic tilt increases while the lumbar spine curvature decreases also during prolonged sitting. These changes can indirectly affects the control of postural and core musculature (Shamsi et al., 2020). Development these abilities can be achieved through regular breaks from prolonged sitting. It is widely accepted that active recovery is superior to passive recovery (Henning et al., 1997; Waongenngarm et al., 2018; Ding et al., 2020), which often includes muscle stretching and strengthening exercises (Macedo et al., 2011; del Pozo-Cruz et al., 2013; Shariat et al., 2018; Sufreshtri and Puspitasari, 2020). However, their specific effects on the recovery of impaired core and postural stability have not been sufficiently investigated so far. Additionally, the question remines as to which of these modalities is more effective and suitable for implementation in workplace conditions.

One of the most frequently used are core stabilization and strengthening exercises. Their goal is to enhance and reinstate the simultaneous contraction and coordination of both global and local muscles (Imai et al., 2014b). Global muscles are connected to the pelvis and hips and are responsible for transferring loads between the thoracic cage and the pelvis, as well as for producing torque (Bergmark, 1989). Local muscles primarily attach directly or indirectly to the lumbar vertebrae (Bergmark, 1989). They play a crucial role in stabilizing the lumbar spine segments, maintaining the lumbar spine in a neutral position, and adjusting functional postures with minimal trunk motions, such as in exercises like the side bridge and back bridge (Imai et al., 2014a). The co-activation, coordination, and neural control of trunk muscles are needed for restoring core and postural stability (Imai et al., 2014b). Evidence supports the efficacy of core stabilization exercises in mitigating muscle fatigue induced by prolonged sitting and static postures (Jackson et al., 2013; Holmes et al., 2015; Kim and Jee, 2020; Saiklang et al., 2021; Salim et al., 2021; Lee et al., 2022; Saiklang et al., 2022a; Saiklang et al., 2022b; Yeom et al., 2023). Trunk stabilization exercises are known to be effective in maintaining core and postural control (Butcher et al., 2007; Durall et al., 2009; Kahle and Gribble, 2009; Imai et al., 2014b). Core exercises, such as McGill stabilization exercises and Brill’s core exercises, have also been found to increase the range of motion actively achieved by the muscles of the back in individuals with chronic low back pain (Cho et al., 2014; Ghorbanpour et al., 2018). This improvement is likely attributed to enhanced coordination among posterior lumbar muscles (Cho et al., 2014; Ghorbanpour et al., 2018).

In the present study, the researcher assumed that foam rolling exercises might improve core and postural stability (Junker and Stöggl, 2019). Foam rolling provides an unstable surface, making it challenging for the body to maintain balance and stability during training. The potential impact on core stability could stem from factors such as the application of one’s own body weight and specific postures during individual exercises, as well as the static effort required during training sessions (Lukas, 2012; Imai et al., 2014a). Though foam rolling exercise are not superior to traditional strengthening exercises on unstable surfaces (Behm et al., 2015), they are sufficient, suitable, and easier to implement for sedentary employees at the workplace.

In addition to improving core and postural stability, these exercises have positive effects on flexibility. The application of foam rolling exercises together with hamstring flexibility improvement (Junker and Stöggl, 2015; Kim and Lee, 2020) could help reduce pathological curves in the spine (Do and Yim, 2018), which, in turn, could lead to improvements in postural stability (Dadfar and Seidi, 2022). Two studies have highlighted the acute effects of foam rolling on muscle flexibility and joint range of motion. Sullivan et al. (2013) showed that a stick roller massage (similar to the principles of foam rolling) leads to an acute increase in hamstring flexibility. Similarly, an acute bout of foam rolling on the quadriceps muscles increased the range of motion of the knee joint (MacDonald et al., 2013). Miller and Rockey (Miller and Rockey, 2006) reported that foam rolling exercises increased hamstring flexibility over an 8-week time period. Although their results indicated gains in range of motion in the intervention group, these values were statistically insignificant when compared to the control group.

When comparing trunk stabilization exercises to foam rolling exercises, a recent study (Zahiri et al., 2022) demonstrated that the traditional prone plank exercise induced lower muscle activation in the dorsal core muscles compared to quadriceps foam rolling. Therefore, individuals seeking time-efficient exercises may still experience back muscle training stress without the need for additional core exercises like planks. While both exercises seem to offer benefits for the recovery of impaired core and postural stability, the fact that foam rolling can be performed independently, without the need for a professional or a second person, adds extra value to this option. Furthermore, it is crucial to recognize that participant motivation and adherence play pivotal roles in achieving successful outcomes with workplace exercises (Kaeding et al., 2017). Performing exercise programs of short duration have been shown (Bell and Burnett, 2009) to improve adherence in employees. Myofascial release is typically recommended to last between 60 and 90 s, up to a maximum of 5 minutes. Various studies support this duration range. One study involved using a roller massager for three sets of 30-s repetitions with 10-s rest intervals, resulting in a 4% increase in ankle range of motion. Another study applied a PVC pipe covered in foam to the quadriceps, conducting two 1-min sessions with 1-min breaks in between, leading to a 12.7% increase in quadriceps range of motion observed 2 minutes after rolling. Additionally, another study examined rolling on the hamstring using different timed intervals: one set for 5 s, one set for 10 s, two sets for 5 s, and two sets for 10 s. This approach yielded a 4.3% increase in range of motion from pre to post-test, with a 2.3% difference observed between 10-s and 5-s intervals (Couture et al., 2015). Employees can take short breaks throughout the day to perform foam rolling routines without disrupting workflow. If foam rolling proves to effectively activate the trunk musculature, it can replace trunk-specific exercises like sit-ups, back extensions, and planks in the workplace (Zahiri et al., 2022). Consequently, training time would reduce (Zahiri et al., 2022), which is a positive aspect for exercise at the workplace. Additionally, research indicates diverse exercise regimens are vital for sustained workplace engagement (Bredahl et al., 2015). Foam rolling’s varied techniques maintain interest and engagement. Employees can perform many different exercises independently, without the need for a coach (Junker and Stöggl, 2019). Furthermore, foam rolling’s massage benefits include relaxation, stress reduction, and improved mindfulness, benefiting mental wellbeing (Wiewelhove et al., 2019). We believe that these exercises, as active breaks, can be successfully implemented to aid in the recovery of impaired core and postural stability in the workplace. These break exercises seem to be capable of restoring muscle strength and flexibility after prolonged sitting, potentially preventing low back pain symptoms in employees.
